Magnetic Resonance (MR) Examinations of the Brain—In addition to evaluating feasibility of TNS treatment for PAE, this study explores possible brain bases of TNS therapy and predictors of clinical response. For these purposes, children undergo an ~60-min examination in a conventional clinical MRI scanner (3 T, 32-channel headcoil). Children are safety screened for MRI contraindications including metal in or on the body or clothing. Children's heads are firmly and comfortably positioned in the scanner with ample head padding. An MRI-opaque Vitamin E capsule is taped to the right scalp to ensure proper left-right lateralization of images in post-processing. Ear plugs are provided to protect against loud scanner noise. Patient and scanner operator have audio contact over a loudspeaker and microphone at all times. The patient also has an emergency squeezebulb to sound an alarm in case of distress. Multiple whole-brain scans are acquired, each in a different MR modality. They include rapid scout structural scans, eyes-open resting-state fMRI (rsfMRI), high-resolution structural MRI, echo-planar spectroscopic imaging (EPSI), and diffusion tensor imaging (DTI). All of these scans are equivalent from a human subjects and safety point-of-view. MRI is acquired by two trained Study Researchers and/or Research Assistants before and after the TNS treatment regimen.

#### In-Treatment Assessments (nightly):

For each overnight session of TNS, the parent makes an entry into the TNS Diary. Purpose is to encourage and to record adherence with the treatment program.

#### In-Treatment Assessments (weekly):

Children's Sleep Habits Questionnaire (CSHQ; Owens et al. 2000)—This is a validated, reliable parent-completed test (~10 min) of a child's sleep quality and sleep behaviors. It is completed by the parent during the pretreatment assessment and at the end of each week of treatment. The CSHQ is reviewed by a Study Researcher.

Side Effects Rating Scale and Adverse Events Inventory (McGough et al. 2015)—These instruments were used by [name] and UCLA colleagues to assess potential side effects of TNS and adverse events in the clinical trials that led to FDA-clearance of TNS as a treatment for unmedicated pediatric ADHD. (Side effects and adverse events were mild and few.) We have slightly modified the Side Effects Rating Scale Parent Version in order to provide a Side Effects Rating Scale Child Version worded in a way more easily understood by children. An open-ended (i.e., non-pre-specified) side effects question has been added to the end of each scale. Both are completed during pretreatment assessment and at the end of each week of treatment in the presence (telephone, Zoom, or in-person) of a study investigator. The Side Effects Rating Scale Parent is completed by the parent. The Side Effects Rating Scale Child is read by the investigator to the child. The Side Effects Rating Scale is reviewed by a Study Researcher; the Adverse Events Inventory is reviewed by the Study Coordinator. Parents and children are generally advised to report serious emergent side effects or adverse events to the Study Coordinator or to a Clinician Investigator ([name]) as soon as possible after occurrence.

#### Post-TNS (Treatment) Assessments:

Conners 4 P (see above)—The parent completes a final Conners 4 P at the end of treatment.

CGI-I (see above)-- A Clinician Investigator administers the CGI-I to the parent at the end of treatment.

ADHD-RS (see above)-- A Clinician Investigator administers the ADHD-RS to the parent at the end of treatment.

BRIEF II (see above)—A Study Researcher administers the BRIEF II to the parent at the end of treatment.

NIH Toolbox (see above)—The Study Coordinator administers the two Toolbox batteries to the child at the end of treatment.

Delis-Kaplan Executive Function System (D-KEFS) Verbal Fluency. As above.

Narrative. As above.

CDI 2. As above.

RCADS. As above.

ARI. As above.

MR Exam (see above)— Two Study Researchers and/or Research Assistants conduct an MRI session at the end of treatment.

#### Follow-Up Assessments:

CGI-I (see above)-- A Clinician Investigator administers the CGI-I to the parent 4 weeks after the end of treatment.

ADHD-RS (see above)-- A Clinician Investigator administers the ADHD-RS to the parent 4 weeks after the end of treatment.

## Primary Study Device

Active TNS is administered nightly for 4 weeks by the parent/caregiver during sleep. Stimulation is performed using the Generation 1.0 Monarch® eTNS® System (NeuroSigma, Inc., Los Angeles), FDA-cleared for unmedicated pediatric ADHD. This device has been used safely and successfully in other prior and ongoing TNS trials at UCLA. The stimulator is worn on the child's pajamas or T-shirt and is attached with thin wires to disposable, silver-gel, self-adhesive patch electrodes. Parents apply patches across their child's forehead to provide bilateral stimulation of both V1 trigeminal branches for ~8 hr nightly. Patches are removed each morning. The active condition uses a 120-Hz repetition frequency, with 250-ms pulse width, and a duty cycle of 30 s on/30 s off. Current settings from 2-4 mA (range 0–10 mA) are established at baseline by titration, which identifies a stimulation level below the patient's subjective level of discomfort. Power is provided by 9-V Li rechargeable medical-grade batteries (iPower v.3), which are checked and replaced regularly. Patients are informed at a scripted presentation that "pulses may come so fast or so slowly that the nerves in the forehead might or might not detect a sensation." Each night parents turn on the device, press the "up" button until stimulation is uncomfortable or until the device reaches maximum current, and then press "down" to decrease it by 1 0.2-mA step. In active devices, the current to the patch is limited to a safe range (0-10 mA). Some patients may feel some sensation, which generally fades with time. The parent/caregiver maintains a TNS Diary to record adherence. The Study Coordinator also keeps in daily contact with the parent/caregiver for this purpose. Weekly, the parent/caregiver completes the BRIEF II, the Children's Sleep Habits Questionnaire (CSHQ; Owens et al. 2000), the Side Effects Rating Scale and Adverse Event Inquiry (McGough et al. 2015), and the Conners 4 Global Impression (Conners 4; Conners 1997), a parent-rated scale of ADHD severity. The CSHQ evaluates whether treatment (positively or negatively) affects the child's sleep. Improvement in sleep quality was a side-benefit of TNS in the ADHD open trial (McGough et al. 2015) and severely disturbed sleep is often seen in PAE. The Study Coordinator asks about any safety or tolerance issues and refers the child, if needed, to a Clinician Investigator for management.

The FDA-clearance for the Monarch TNS device covers only children with ADHD who are not currently taking ADHD medication. Children with ADHD associated with PAE are not specifically excluded by the labelling, nor are they specifically included. This proposal will test the TNS device in children with ADHD associated with PAE, some of whom will be taking concurrent ADHD medication. Based on our Initial Assessment, we do not anticipate additional risks due to medication and we will not ask parents to take their children off medication. Thus, TNS treatment, at least for children on medication, will be off-label. Therefore, rather than as "treatment with a n FDA-cleared device within an approved indication", present research is classified as "investigational use of an NSR device".

This is a feasibility study. One goal is to assess the tolerability of TNS treatment in children with ADHD and PAE. One key question here is whether children will remove the TNS device overnight unbeknownst to their parents? Studies of TNS treatment of pediatric ADHD at UCLA to date are encouraging in that there have *not* been issues with children removing the device in these studies. In principle, however, it could be different for children with ADHD and PAE. In our study, parents of each child are given a TNS Instructions and FAQ document at the beginning of treatment. Among several troubleshooting tips, parents are advised what to do if their child removes the device. If they catch it in the course of the night, they are advised to replace the device with fresh electrodes. If they do not become aware until the next morning, they are advised to note the incident in the TNS Diary and to contact the study team. When reapplying the device the next evening, parents are advised that putting a headband over the electrodes may help, especially if the child is a restless sleeper. Additionally, the parents should ensure that no lotions or creams, that may facilitate slippage, are applied to the skin under or around the electrode. This information is also given to parents verbally at time of TNS instruction.

Per the study design, *TNS compliance* is defined as the child wearing the device for 21 of 28 nights of treatment. Thus, non-compliance is failure to wear the device for 7 hours or more on 8 or more nights during the treatment regimen. In such cases, we will contemplate investigator-withdrawal of the child from the study. Among other factors, the decision to withdraw a child will be made based on interim scores on the Conners 4, i.e., does the patient appear to be getting better, despite partial non-compliance? In the TNS Instructions and FAQ document and on the ICF, parents are informed that their child may be withdrawn from the study if he or she repeatedly removes the device overnight or otherwise fails to comply with study procedures. Although we use the figure of 8 nights as an investigators' guidepost, we do not give a specific number in the TNS Instructions or ICF. This is because we feel that, if we did, some parents might think it is "okay" to skip 8 nights of treatment or might misreport the numbers of or fail to report incidences of removing the device for fear their child being withdrawn from treatment. For what we really want is to encourage 100% compliance and to work with families who are having difficulties reaching that benchmark.

We will tally compliance and numbers of subjects withdrawn. Efficacy statistics will be computed twice. We will compute them once for all patients, completers and withdrawn. Thereby, we will use last observation carried forward (LOCF) for cognitive and symptom scores of patients withdrawn. We will compute efficacy statistics again for completers only. The results of both computations are useful and relevant. The former mitigates against bias in rejecting non-responders. The latter tells what efficacy is if compliance is achieved, a reasonable goal in most cases.

The investigators will withdraw any participant from the study who, in the judgement of the Study Physician, experiences excessive risk (e.g., serious side-effects) or who requires prompt care (e.g., discovery of a serious incidental finding) that is incompatible with continued participation.

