  6. Post-TNS Assessment in completers within 1 week of completing TNS; same assessments as Pre-TNS
    - a. Height, weight, and vitals of the child are taken
    - b. The CGI-I and the ADHD-RS are administered by a Clinician Investigator to measure baseline ADHD symptoms
    - c. The NIH Toolbox is administered by the Study Coordinator to probe the Cognition and Emotional Control behavioral domains
    - d. The BRIEF II is administered to measure executive functions
    - e. The Conners 4 is administered to measure inattention and impulsivity/hyperactivity
    - f. The D-KEFS Verbal Fluency battery is administered to the child
    - g. The Test of Narrative Language is administered by the Study Coordinator to assay language impairments
    - h. The CDI 2 is administered to assess depressive symptoms and possible suicidality as a withdrawal criterion
    - i. The RCADS is administered to assess anxiety and depression symptoms
    - j. The ARI is administered to assess irritability
    - k.
  7. Post-TNS MRI to be performed maximum 1 week after completing TNS treatment
  8. 4 weeks after completing TNS, patients undergo Follow-Up Assessment, consisting of the CGI-I and the ADHD-RS.

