#### Measurements:

1. Primary outcome: Score on the ADHD-RS, a clinician-rated measure of severity of core symptoms of ADHD; administered pre- and post-TNS
2. Secondary outcome: Score on the CGI-S/CGI-I ADHD, clinician-rated measures of severity of core symptoms of ADHD; CGI-S is administered pre-TNS and CGI-I is administered post-TNS
3. Magnetic Resonance Imaging: multiple modalities and endpoints, acquired pre- and post-TNS

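### Completers are not the same as compliers, so the completers-only analysis does not show efficacy under compliance as the protocol says it does

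*Protocol*

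**What the plan says.** The compliance paragraphs under Primary Study Device in the Protocol do three things.

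- They define compliance by wear: "defined as the child wearing the device for 21 of 28 nights of treatment". Non-compliance is put as eight or more nights on which the device was not worn for at least 7 hours.
- They make withdrawal of a non-compliant child discretionary and allow interim response to count: "Among other factors, the decision to withdraw a child will be made based on interim scores on the Conners 4". The question posed is whether the child seems to be improving in spite of poor wear.
- They plan two efficacy computations, one in all patients with last observation carried forward (LOCF) for those withdrawn, and one in completers. Of the second they say: "The latter tells what efficacy is if compliance is achieved". Data Analysis repeats the two computations. Neither section names a set defined by nights worn.

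The primary outcome, under Measurements, is the ADHD-RS, "a clinician-rated measure of severity of core symptoms of ADHD; administered pre- and post-TNS". The Timeline places it at weeks 0, 5 and 9. The weekly interim scales in Research Protocol item 5e include the Conners 4 and BRIEF II but not the ADHD-RS. Item 6 of the same section reads "Post-TNS Assessment in completers within 1 week of completing TNS", and item 8 "4 weeks after completing TNS, patients undergo Follow-Up Assessment".

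**The concern.** Completers are compliers plus those non-compliant children who were kept, and they were kept partly because a scale of the same core symptoms as the primary outcome looked favourable. A figure from that group does not describe what happens when the device is worn as intended, although the protocol gives it that meaning.

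Two things are at stake. Promising efficacy is part of the Aim 1 feasibility hypothesis, and this pilot is meant to support an application for a sham-controlled trial, so its efficacy figures should mean what they are said to mean. Second, the protocol relies on the all-patient analysis to guard against the loss of non-responders, and that guard is weaker for the ADHD-RS than it appears. A later analysis plan could define a nights-worn set, but it could not recover week 5 and week 9 scores that were never collected.

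**Working it through.** **Stated figures.** Fewer than 21 of 28 nights means at least 28 - 21 + 1 = 8 missed nights, so the two thresholds agree. The 30 enrolled and 24 after attrition imply 1 - 24/30 = 20% attrition. No stated number is wrong; the fault lies in the interpretation.

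**Size of the bias.** The protocol gives no non-compliance rate, no correlation between scales and no weight for the Conners 4, so the following are assumptions:

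- q, the non-compliant share: 20-40%, with 10% as a lower case.
- r, the correlation of interim Conners 4 change with final ADHD-RS change: 0.5-0.7.
- a and b, the probability that a non-compliant child is withdrawn if not improved and if improved: 0.75 and 0.25 (partial rule), or 1 and 0 (strict rule, an upper bound). Improved means an interim change above 0.
- dc and m, the mean change in compliant and non-compliant children, in SD of change, with the same m on both scales.

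With Phi and phi the normal distribution function and density at m:

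- s = (1-b)(m·Phi + r·phi) + (1-a)(m·(1-Phi) - r·phi)
- k = (1-b)·Phi + (1-a)·(1-Phi)
- completer mean = ((1-q)·dc + q·s) / ((1-q) + q·k)

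Example: q = 0.4, r = 0.5, partial rule, dc = 0.5, m = 0. Then s = 0.5 × 0.5 × 0.3989 = 0.0997 and k = 0.5. The completer mean is (0.6 × 0.5 + 0.4 × 0.0997) / (0.6 + 0.4 × 0.5) = 0.340/0.80 = 0.425, against 0.50 in compliant children.

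Completer mean minus complier mean under the partial rule, in SD (each range runs over r = 0.5 to 0.7):

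| Change in compliers / non-compliers | q = 10% | q = 20% | q = 40% |
|---|---|---|---|
| 0 / 0 | +0.010 to +0.015 | +0.022 to +0.031 | +0.050 to +0.070 |
| 0.5 / 0.5 | +0.009 to +0.013 | +0.019 to +0.027 | +0.042 to +0.059 |
| 0.5 / 0.25 | -0.004 to 0.000 | -0.009 to 0.000 | -0.020 to -0.001 |
| 0.5 / 0 | -0.016 to -0.012 | -0.033 to -0.025 | -0.075 to -0.055 |

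Under the strict rule at 20-40%, the four rows become +0.04 to +0.14, +0.04 to +0.11, +0.01 to +0.06, and -0.025 to +0.015. Under the partial rule, non-compliant children make up 11-13% of completers at q = 20% and 25-28% at q = 40%.

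For scale, the standard error of a mean change at n = 24 is 1/√24 = 0.204 SD. The largest partial-rule bias is 0.075/0.204 = 0.37 of that; at q = 10% it is 0.016/0.204 = 0.08.

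**All-patient analysis.** A child withdrawn during treatment has an ADHD-RS at week 0 only, so LOCF enters a change of zero. The LOCF mean is then (1-q)·dc + q·s, against (1-q)·dc + q·m had everyone been assessed. In the example these are 0.340 and 0.300. Across the partial-rule settings at 20-40% the difference runs from -0.05 to +0.06 SD. The CGI-I is first given after treatment, so it has no earlier value to carry. LOCF does have in-treatment values for the weekly Conners 4 and BRIEF II, and no figure is claimed for those.

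**The case against.** The strongest reply is that little turns on this. It is an open, uncontrolled pilot of 30 children, rigorous efficacy testing is left to a later trial, and no decision rule is tied to the completer estimate. The Conners 4 is one factor among several, withdrawal is only contemplated, and a child who reaches the eighth failed night late has little treatment left to be withdrawn from. The protocol reports no problem with device removal in earlier ADHD studies at the same centre, though it allows that these children may differ. At q = 40% the partial rule would by itself withdraw 0.4 × (1 - k), or 16-20% of all children, close to the whole 20% attrition allowance, so the upper end of the range is generous. Nightly wear is recorded in the diary, so a nights-worn set can be built. Keeping a child who seems to benefit is also a defensible judgement and avoids a missing outcome. All of this stands, and it limits the size of the point. It does not make the stated interpretation correct.

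Two stronger readings go too far. A reader might infer that the rule inflates efficacy. That follows if there is no effect, or if benefit does not depend on wear; if poor wearers benefit less, the bias can be near zero or negative, and the protocol cannot say which applies. A reader might also infer that assessment of withdrawn children is left open, because other sections say "A Clinician Investigator administers the ADHD-RS to the parent at the end of treatment" and "A Clinician Investigator administers the ADHD-RS to the parent 4 weeks after the end of treatment" with no limit to completers. Those entries state who gives which scale and when; they do not define a population. Item 6 of Research Protocol, read with the LOCF rule, points to no post-treatment ADHD-RS for withdrawn children, although the protocol never says so outright.

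**Conclusion.** The point holds as an error of interpretation: by the protocol's own 21-night definition, the completer analysis does not estimate efficacy under compliance. This conclusion needs no assumed figure. The numerical consequence is probably small and of unknown sign, at most 0.075 SD of change in either direction under the partial rule at 20-40% non-compliance. That range rests wholly on the assumed rate, correlation, withdrawal probabilities and effects. The all-patient analysis offsets the problem only in part, because its ADHD-RS values for children withdrawn during treatment would be baseline scores. The point is worth correcting because the correction is cheap and scores not collected cannot be recovered later.

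**What to change.** 1. Define the efficacy-under-compliance set as children who wore the device on at least 21 of 28 nights, using the diary data, and describe the completer analysis as children who stayed in the study. This costs only wording, since the data are already collected.
2. State that ADHD-RS and CGI-I at weeks 5 and 9 will be sought by parent interview from every child who started TNS, including those withdrawn, where the family agrees, and use the observed scores in the all-patient analysis. This costs a few extra interviews. Families of investigator-withdrawn children already receive full payment, so those terms need not change.
3. Preferably, base withdrawal for non-compliance on wear and safety rather than interim efficacy scores, leaving safety withdrawals as they are. The price is less investigator discretion, and possibly losing a child who seems to benefit. This step is secondary once the first two are in place.

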## Generation 1.0 NeuroSigma Monarch® eTNS® System

### Main component

*Monarch* (external pulse generator)

1. LCD Screen
2. Output Ports (CH1, CH2)
3. Up Key
4. Down Key
5. Lock Key
6. SELECT Key
7. ON/OFF Key
8. SET Key
9. Battery Cover

[figure not shown]

The Monarch eTNS System is designed to deliver electrical stimulation to the V1 branches of the trigeminal nerve, located just under the skin above the eyebrows, *via* a cutaneous electric patch.

The trigeminal nerve carries somatosensory information from the face to the brain. External trigeminal nerve stimulation (TNS) uses this pathway to send therapeutic stimulation into the brain. The trigeminal nerve connects from the face to the brainstem, and from there to other brain regions implicated in inattention, hyperactivity, and executive function deficits. While the exact mechanism of TNS is unknown, neuroimaging studies show that TNS increases activity in regions associated with regulating attention, emotion, and behavior.

[figure not shown]

## Back-Up Study Device

The Generation 2.0 Monarch® eTNS® System, also manufactured by NeuroSigma, is the back-up study device. By “back-up” we mean we intend to use the Gen 1 Monarch® for all 30 subjects for their full 4-week treatment regimens. The Gen 1, however, is being phased-out to be replaced with the Gen 2 starting in January 2025. We will be using brand-new Gen 1 devices. Nonetheless it is conceivable that one or more of our stock of Gen 1 devices will become unavailable or unusable due to damage, loss, theft, etc., and NeuroSigma will be unable to supply a new Gen 1 to replace it. Whenever this is the case, we will replace it with a Gen 2 in order to complete all or part of a patient’s regimen. Therefore, we are requesting approval to use the Gen 2 as a therapeutically equivalent ersatz.

The brochure, manual, and FDA-clearance letter for the Generation 2.0 Monarch eTNS system are attached. The Gen 2 has nearly identical electrical parameters as the Gen 1. In particular, the Gen 2 delivers the same electric current and voltage stimulation waveforms to the patient. One small difference in electrical parameters between the two devices are that the Gen 2 has an output current range of 0–8 mA rather than 0–10 mA for the Gen 1. This was changed because few patients used the upper end of the range. The other small difference is that the Gen 2 output current is adjustable in increments of 0.1 mA, rather than 0.2 mA for the Gen 1. This was done to afford the patient, caregiver, or clinician higher precision in adjusting the instrument. Rather than in electrical parameters, the Gen 2 mainly differs from the Gen 1 in having a slimmer form factor and user-friendlier software interface. If anything, these modifications render the Gen 2 even safer than the Gen 1.

The Gen 2 has the same FDA-clearance as the Gen 1. The PI has made an Initial Assessment that the Gen 2 device merits a classification as a non-significant risk (NSR) device. In this proposal we ask the IRB to agree or disagree with this classification. This IRB has already agreed with an NSR classification for the Gen 1 device.

Other study-related aspects of the Gen 2 are identical to those of the Gen 1 as described above.

Generation 2.0 NeuroSigma Monarch® eTNS® System

|                                                                                                                                                                                                                                                                                                                                                                                                                                        |                                                                                                                                                                                                                                                                         |
|----------------------------------------------------------------------------------------------------------------------------------------------------------------------------------------------------------------------------------------------------------------------------------------------------------------------------------------------------------------------------------------------------------------------------------------|-------------------------------------------------------------------------------------------------------------------------------------------------------------------------------------------------------------------------------------------------------------------------|
| [figure not shown] 
A white, rectangular external pulse generator with a black screen at the top. The screen displays '3.0' in large orange digits, a battery icon, and the text 'Press O to Go'. Below the screen, the word 'MONARCH' is printed in blue. Further down, there are three large blue symbols: a plus sign (+), a circle (O), and a minus sign (-).
 | [figure not shown] 
A hand holding the white Monarch eTNS system. The device's screen shows '3.0' and 'Press O to Go'. The hand is positioned to show the device's size relative to a human hand.
 |
| 
A) The Monarch Gen 2.0 external pulse generator
                                                                                                                                                                                                                                                                                                                                                                                 | 
B) B) The Gen 2.0 Monarch eTNS System held in a representative human hand for scale.
                                                                                                                                                                             |
| [figure not shown] 
A blue, rectangular cutaneous electrical patch with a white wire attached, lying next to the white Monarch eTNS system. The device's screen shows '3.2' and 'Press O to Start'. The patch is connected to the device via the white wire.
                                                                                                   |                                                                                                                                                                                                                                                                         |
| 
C) The Monarch NS-2 external (cutaneous) electrical patch beside the Gen 2.0 Monarch eTNS System.
                                                                                                                                                                                                                                                                                                                               |                                                                                                                                                                                                                                                                         |

